#### Provisions for post-trial care {30}

There will be no formal provision of the intervention beyond the trial period, as recommended by the World Health Organization (WHO) interim guidance that any specific therapy targeted to SARS-CoV-2 infection should be provided only as part of a research protocol [12]. All subsequent requirement of both SARS-CoV-2 and unrelated needs will be under the existing healthcare system in the recruiting centres.

#### Outcomes {12}

The co-primary outcomes are:A between-group difference in d-dimer levels over time, assessed by measurement of area under the curve (AUC) on days 1, 3, 5 and 10A between-group difference in the occurrence of serious adverse events (SAEs) as listed in the safety analysis

Secondary efficacy outcomes include analysis of between-group differences in:Oxygenation index (OI) = (FiO_2_ × M_PAW_)/PaO_2_ will be recorded every 6 hPulmonary compliance will be recorded every 6 h up to day 10 in invasively ventilated patientsDynamic pulmonary compliance is measured automatically on our ventilators (Puritan Bennett and Servo I) and recorded on the ICU Clinical Information System), measured as ∆V/∆PInflammatory and coagulation markersIL-1β, IL-6, IL-8, IL-10, soluble tumour necrosis factor receptor 1, C-reactive protein, procalcitonin, ferritin, fibrinogen and lactate dehydrogenase LDH will be assessedAUC measurement for these inflammatory and coagulation markers on days 1, 3, 5 and 10Ratio of IL-1β/IL-10 and IL-6/IL-10Time to separation from invasive ventilation to day 28, where non-survivors to day 28 are treated as though not separated from invasive ventilation, measured in daysNumber tracheotomised to day 28 (*N*)Time to separation from the ICU to day 28, where non-survivors to day 28 are treated as though not separated from invasive care measured in daysSurvival to day 28, survival to day 60 and survival to hospital discharge, censored at day 60

Additional outcomes include:Time to separation from invasive ventilation to day 28, among survivorsNumber treated with neuromuscular blockers instituted after enrolment to day 10Any administration of neuromuscular blocking drugs will be recordedNumber treated with prone positioning instituted after enrolment to day 10Number treated with extra-corporeal membrane oxygenation instituted after enrolment to day 10Time to separation from the ICU to day 28, among survivors, measured in daysNumber residing at home or in a community setting at day 60Number residing at home or in a community setting at day 60, among survivors

Safety outcomes include analysis of between-group differences in:Air quality samples from an infection control perspective (A TSI optical particle sizer device will be used to collect data on fugitive aerosol emissions during nebulisation, and throughout randomly selected 24-h periods in intubated and non-intubated patients, and in control and treatment arm patients.) This will be a descriptive analysis of air quality information in a selected number of patients.Number of patients transfused red blood cells to day 10Volume of red blood cells transfused to day 10Number who record major bleeding to day 10‘Major bleeding’ is defined as bleeding that results in death and/or bleeding that is symptomatic and occurs in a critical area or organ (intra-cranial, intra-spinal, intra-ocular, retroperitoneal, intra-articular or intramuscular with compartment syndrome) and/or bleeding that results in a fall in haemoglobin of 20g/l or more, or results in transfusion of two or more units of whole blood or red cells [13]Number of patients who record clinically relevant non-major bleeding as defined by the International Society on Thrombosis and Haemostasis [14]Number who record a diagnosis of heparin-induced thrombocytopenia (HIT)Number who record other adverse events and reactionsAdverse events will be assessed systematically with patient and chart reviews on a daily basis, with all clinical events reviewed and assessed by the investigator, and adverse events recorded and reported appropriately. AEs will be classified by organ system

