### Eligibility criteria {10}

Patients with confirmed SARS-CoV-2 infection receiving advanced respiratory support in an intensive care environment. See Table 1.

**Table 1 Tab1:** Eligibility criteria for participants

Inclusion criteria	Exclusion criteria
Confirmed or suspected COVID-19 If ‘suspected’, results must be pending or testing intended	Enrolled in another clinical trial that is unapproved for co-enrolment
Ability to obtain informed consent/assent to participate in study	Heparin allergy or heparin-induced thrombocytopenia
Age 18 years or older	APTT > 100 s
Requiring high-flow nasal oxygen (>30l/min) or positive pressure ventilator support or invasive mechanical ventilation in the ICU for a time period of no greater than 48 h	Pulmonary bleeding, which is frank bleeding in the trachea, bronchi or lungs with repeated haemoptysis or requiring repeated suctioning
D-dimers > 200 ng/ml	Platelet count < 50 × 10^9^ per l
Acute opacities on chest imaging affecting at least one lung quadrant. ‘Acute opacities’ do not include effusions, lobar/lung collapse or nodules	Uncontrolled bleeding
Currently in a higher level of care area designated for inpatient care of patients where therapies including non-positive pressure ventilatory support (e.g. high-flow nasal oxygen) can be provided	Pregnant or suspected pregnancy (urine or serum HCG will be recorded)
	Receiving or about to commence ECMO or HFOV
	Myopathy, spinal cord injury or nerve injury or disease with a likely prolonged incapacity to breathe independently, e.g. Guillain-Barre syndrome
	Usually receives home oxygen
	Fully dependent on others for personal care due to physical or cognitive decline prior to this illness (premorbid status)
	Death is imminent or inevitable within 24 h
	The clinical team would not be able to set up the study nebuliser and ventilator circuit as required including with active humidification
	Clinician objection
	The use or anticipated use of nebulised tobramycin during this clinical episode
	Any other specific contraindication to anticoagulation including prophylactic anticoagulation not otherwise listed here
	Relapse in clinical condition requiring advances respiratory support in patient that had fully weaned from advanced respiratory support
	Receiving any direct/novel oral anticoagulant

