#### Criteria for discontinuing or modifying allocated interventions {11b}

Outlined in Table 2.

**Table 2 Tab2:** Indications for withholding and recommencement of nebulised heparin

Nebulised heparin should be withheld if any of the following occurs:	Nebulised heparin should be recommenced if:
More than 10 days have elapsed since randomisation	Having been withheld because the patient was outside the ICU, the patient returns to ICU
The patient is outside of higher-level care setting	Having been withheld because the patient was not receiving advanced respiratory support, advanced respiratory support is reinstituted
The patient is not receiving advanced respiratory support	Having been withheld because the APTT was unacceptably prolonged, the APTT becomes acceptable
The treating physician deems that there is a clinically unacceptable increase in APTT (>100s)	Having been withheld because there was excessive bloodstaining of respiratory secretions, the bloodstaining of the respiratory secretions has resolved
The treating physician deems that there is excessive bloodstaining of respiratory secretions	Having been withheld for suspected HIT, the patient is found not to have this condition
There is pulmonary bleeding, major bleeding or suspected or confirmed HIT	Having been withheld for ECMO, the treatment with ECMO is stopped
The patient is receiving ECMO or HFOV	Having been withheld for HFOV, the treatment with HFOV is stopped

Each participant has the right to withdraw from the trial at any time. Where the participant gives a reason for withdrawal (they are not obliged to provide a reason), the reason for withdrawal will be recorded. Equally, the investigator may decide to withdraw a patient from the study at any time — in this case, the reason for withdrawal will be recorded. If a patient withdraws from the study, they will be encouraged to complete the follow-up aspect of the study. Also, if a patient withdraws from the study due to a safety event, mandatory follow-up of that event until its resolution will occur.

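### Pulmonary bleeding is defined and is a reason to withhold nebulised heparin, but it is not counted as its own safety outcome, and the adverse event rules may not capture it equally in both arms

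*Protocol article*

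**What the plan says.** Table 1 (Eligibility criteria {10}) excludes patients with "Pulmonary bleeding, which is frank bleeding in the trachea, bronchi or lungs with repeated haemoptysis or requiring repeated suctioning". This is the only definition of the term in the article.

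Table 2 (Criteria for discontinuing or modifying allocated interventions {11b}) gives as one reason to withhold: "There is pulmonary bleeding, major bleeding or suspected or confirmed HIT". A separate row adds: "The treating physician deems that there is excessive bloodstaining of respiratory secretions".

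The safety list under Outcomes {12} names air quality, red-cell transfusion (patients and volume), major bleeding, clinically relevant non-major bleeding, heparin-induced thrombocytopenia (HIT), and other adverse events and reactions. Major bleeding covers "bleeding that results in death and/or bleeding that is symptomatic and occurs in a critical area or organ", the areas being "intra-cranial, intra-spinal, intra-ocular, retroperitoneal, intra-articular or intramuscular with compartment syndrome", and also "bleeding that results in a fall in haemoglobin of 20g/l or more, or results in transfusion of two or more units". The definition is attributed to a cited source. The non-major category is given by citation only: "Number of patients who record clinically relevant non-major bleeding as defined by the International Society on Thrombosis and Haemostasis". For the rest, "AEs will be classified by organ system".

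The section on procedures for recording adverse events (under {22}) contains two rules. The first puts every adverse event on the eCRF regardless of attribution. The second, a few lines later, limits routine recording of non-serious events to those judged related to the investigational product, up to 96 h after the last dose. Serious adverse events (SAEs) are reported without such a limit, and a between-group difference in SAEs is a co-primary outcome.

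**The concern.** Heparin is nebulised into the airway every 6 hours, 25,000 I.U. at a time, so airway bleeding is a natural local harm to tabulate in a phase 1b/2a trial with safety as a co-primary aim. The protocol itself treats it as a distinct hazard, since it defines the event and acts on it. Yet no outcome row gives the number of patients affected in each arm.

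At stake is a plain question that readers of the results will ask: how many patients bled into the airway with nebulised heparin, and how many without it? Pooled all-site rows cannot answer it. If the narrower recording rule is followed, the control figure for milder events is incomplete as well.

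**Working it through.** The article states no figure on this point, so there is none to reproduce. The check is mainly a reading of the passages side by side.

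**Step 1: the items on one Table 2 line against the safety outcomes.**

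| Table 2 item | Defined in the article | Own row in the safety outcomes |
|---|---|---|
| Pulmonary bleeding | Yes (Table 1) | No |
| Major bleeding | Yes (Outcomes {12}) | Yes |
| HIT | Named, not defined | Yes |

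Pulmonary bleeding is the only item on that line without its own outcome.

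**Step 2: where an airway bleed is counted.** Take a bleed that meets the Table 1 definition.

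- Fatal: major bleeding, at any site.
- Haemoglobin fall of 20 g/l or more, or two or more units transfused: major bleeding, at any site.
- Symptomatic but none of these: not major, because none of the six listed areas is the lung or airway. It can enter clinically relevant non-major bleeding, pooled over all sites, or other adverse events classified by organ system.
- Serious by the SAE criteria: also in the SAE co-primary, again pooled with other events.

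Every path leads to some row, but none leads to a count of pulmonary bleeding.

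**Step 3: whether collection is the same in both arms.** Control patients receive no study drug (Intervention description {11a}), so their events cannot be drug-related and they have no last dose from which to count 96 h.

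| Non-serious airway bleed | Rule 1 (all events) | Rule 2 (drug-related only) |
|---|---|---|
| Heparin arm, judged related | Recorded | Recorded |
| Heparin arm, judged unrelated | Recorded | Not routinely |
| Control arm | Recorded | Not routinely |

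Under rule 2 the adverse event row favours finding such bleeds in the heparin arm. Classification by organ system does not repair that.

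**Step 4: size, by illustration only.** The input from the article is 20 patients per arm (Sample size {14}). The event counts and rates are assumptions.

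- Suppose 2 of 20 heparin patients have a pulmonary bleed below the major criteria. The observed proportion is 2/20 = 10%. The exact (Clopper-Pearson) 95% limits solve P(X ≥ 2) = 0.025 and P(X ≤ 2) = 0.025 for n = 20, giving about 1.2% to 31.7%.
- If there were no other major bleeds, the major bleeding row would read 0/20, with upper limit 1 − 0.025^(1/20) = 16.8%. That row is correct by its definition, but it does not describe airway bleeding.
- The chance of at least one event among 20 is 1 − (1 − p)^20: 33% at p = 2%, 64% at 5%, 88% at 10% and 99% at 20%.
- For x/20 against 0/20, the two-sided Fisher p-value is 2·C(20,x)/C(40,x). For x = 4 it is 2 × 4,845/91,390 = 0.106. For x = 5 it is 2 × 15,504/658,008 = 0.047.

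Only a handful of events can be expected, and at least five against none are needed for p < 0.05. Spreading them over several pooled rows makes a pattern harder to see.

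**The case against.** The strongest reply is that nothing is lost. The safety section promises daily patient and chart review. Bleeds below the major threshold belong in the non-major row, serious ones are reported within 24 h and reviewed by the data safety monitoring committee, and adverse events are sorted by organ system. A withholding criterion need not be an outcome: APTT above 100 s and HFOV are also Table 2 reasons without rows. The safety outcomes are said to include those listed, and the article is a summary whose CRF is not shown.

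Most of this stands, and it rules out several stronger readings that a reader might infer:

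- **That airway toxicity could go unseen, or that some share of the heparin arm would be missed.** The documents do not support this. Step 2 shows that every such bleed can enter at least one reported category, and absence from the major bleeding row alone is not a loss.
- **That leaving the lung off the critical-site list is an error.** The list comes with a cited definition that is not at hand, so no error can be shown.
- **That tolerability has no measure.** The abstract defines safety and tolerability by the number of severe adverse events.
- **That withholding is untracked.** The daily heparin dose is collected (Participant timeline {13}), action taken is recorded with each adverse event, and adherence issues are to be reported ({11c}).

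Two things remain. Capture in a pooled row is not a count of the event. And the assurance that milder bleeds are captured depends on the adverse event rules, which disagree about control patients. The article states both rules, so its being condensed does not explain the conflict.

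**Conclusion.** The point holds in a limited form. Pulmonary bleeding is captured, but it is not separately counted, and for non-serious events it may not be fairly compared between arms. The first part follows directly from Tables 1 and 2 and the safety list. The second depends on which recording rule is followed: under the all-events rule the imbalance disappears, and under the drug-related rule it is built in.

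The size cannot be stated from the document, which gives no pulmonary bleeding rate; 2 of 20 is an assumed illustration with a very wide interval. Whether the cited non-major definition takes in every bleed of the Table 1 kind could not be checked. This is a worthwhile, inexpensive improvement to the reporting of a co-primary safety aim, not a flaw that invalidates the safety assessment.

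**What to change.** 1. Add to the safety outcomes the number of patients with pulmonary bleeding to day 10, using the Table 1 definition. Collect it identically in both arms, and report it whether or not the event also meets the major bleeding criteria.
2. Reconcile the two adverse event recording rules, so that it is clear which non-serious events are recorded and that the same applies to control patients.
3. Leave the cited major bleeding definition and the Table 2 withholding rules as they are.
4. Optional: tabulate heparin withholding by Table 2 reason, which would also show the bloodstaining trigger. Dose, action taken and adherence issues are already recorded or reported, so this adds less.

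Cost: one eCRF item and one table row, filled from charts already reviewed daily, with no extra procedure or patients. It would be handled as an amendment under {25}. Recruitment began in December 2020 and was expected to finish in Spring 2022, so patients already enrolled would need retrospective chart review. That review should use the same rules in both arms and be settled before results by arm are seen.

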#### Participant timeline {13}

*Day 0*: screening, consent/next of kin assent, enrolment and randomisation

*Day 1*: The following baseline data will be recorded on the baseline electronic case report form (eCRF):

- Eligibility criteria

- Intubation date and time and intubation setting

- Birth date, sex, height and weight

- History of tobacco smoking, hypertension, diabetes mellitus, asthma and chronic obstructive pulmonary disease

- Hospital admission date, ICU admission date and time, and acute physiology and chronic health evaluation (APACHE) III score, ICU diagnosis

-Treatment in the 24 h prior to randomisation with unfractionated heparin, intravenously or subcutaneously; LMWH, intravenously or subcutaneously; lopinavir-ritonavir; remdesivir; hydroxychloroquine; interferon-β; interleukin antagonists; oseltamivir, laninamivir, zaninamivir or peramivir; macrolide; non-macrolide antibacterial; antifungal; and corticosteroid

- Treatment at the time of randomisation with inotrope or vasopressor infusion, renal replacement therapy, neuromuscular blocker and prone positioning

- Serum creatinine and bilirubin, blood haemoglobin, white cell count and platelet count, blood activated partial thromboplastin time (APTT) and international normalised ratio (INR), collected closest to and before randomisation

- For the chest radiograph or computerised tomography (CT) of chest performed closest to and before randomisation: the number of lung quadrants with acute opacities that are not fully explained by effusions, lobar/lung collapse or nodules; whether the opacities are present bilaterally; whether, given all the medical information about the patient, the opacities are entirely attributable to cardiac failure or fluid overload; and whether there is objective evidence to exclude the possibility of cardiac failure or fluid overload

- Arterial blood gas (pH, PaCO2, PaO2, bicarbonate and lactate) and corresponding ventilation parameters (respiratory rate, FIO2, peak airway pressure, positive end expiratory pressure (PEEP) or continuous positive airway pressure (CPAP) and tidal volume) closest to and before randomisation

*Days 0 to 10*: The following data are gathered from health records at the treating institution:

- Type of respiratory support — high-flow nasal O_2_ (>30l/min)/non-invasive ventilation/invasive mechanical ventilation

- Dose of nebulised unfractionated heparin

-Treatment with unfractionated heparin, intravenously or subcutaneously; LMWH, intravenously or subcutaneously; lopinavir-ritonavir; remdesivir; hydroxychloroquine; interferon-β; interleukin antagonists; oseltamivir, laninamivir, zaninamivir or peramivir; macrolide; non-macrolide antibacterial; antifungal; corticosteroid; inotrope or vasopressor infusion; renal replacement therapy; neuromuscular blocker; prone positioning; and extra-corporeal membrane oxygenation

- Volume of packed red cells and whole blood transfused

- Highest APTT

- Blood samples will be collected for inflammatory marker and coagulation parameter assessment as per the primary and secondary outcomes, on days 0, 3, 5 and 10

*Day 28*: The following data are gathered from health records at the treating institution and, where necessary, other healthcare providers:

- Date of first diagnosis of COVID-19 (clinical diagnosis)

- Date of first positive respiratory sample for SARS-CoV-2 and the sample type

- Acute hospital discharge status at day 28 and, if discharged, the date of discharge and discharge destination including deceased

- Readmission to ICU during the acute hospital admission and prior to day 28

- ICU status at day 28 and, if not in the ICU at the end of day 28, the final date and time of ICU discharge

- Invasive ventilation status at day 28 and, if not receiving invasive ventilation at the end of day 28, the final date and time that invasive ventilation was stopped

- Tracheotomy and, if performed, the procedure date

*Day 60*: The following data are gathered from health records at the recruiting institution and, where necessary, other healthcare providers and the patient or proxy:

- Vital status at day 60 and, if deceased, the date of death and whether death related (directly or indirectly) to COVID-19 infection

- Place of residence at day 60

- If not discharged from the acute hospital discharge status by day 28, the acute hospital discharge status at day 60 is ascertained and, if now discharged, the date of discharge and the discharge destination including whether deceased.

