**Methods:**

This is a multi-centre, phase 1b/IIa, randomised, parallel-group, open-label study. The study will randomise 40 SARs-CoV-2-positive patients receiving advanced respiratory support in a critical care area. Randomisation will be via 1:1 allocation to usual care plus nebulised unfractionated heparin 6 hourly to day 10 while receiving advanced respiratory support or usual care only. The study aims to evaluate whether unfractionated heparin will decrease the procoagulant response associated with ARDS up to day 10. The study will also assess safety and tolerability of nebulised heparin as defined by number of severe adverse events; oxygen index and respiratory oxygenation index of intubated and unintubated, respectively; ventilatory ratio; and plasma concentration of interleukin (IL)-1β, IL6, IL-8, IL-10 and soluble tumour necrosis factor receptor 1, C-reactive protein, procalcitonin, ferritin, fibrinogen and lactate dehydrogenase as well as the ratios of IL-1β/IL-10 and IL-6/IL-10. These parameters will be assessed on days 1, 3, 5 and 10; time to separation from advanced respiratory support, time to discharge from the intensive care unit and number tracheostomised to day 28; and survival to days 28 and 60 and to hospital discharge, censored at day 60. Some clinical outcome data from our study will be included in the international meta-trials, CHARTER and INHALE-HEP.

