#### Intervention description {11a}

Participants assigned to ‘nebulised heparin’ will receive 5ml heparin sodium 5000 I.U./ml (25,000 I.U. in 5 ml), manufactured by Pinewood laboratories, Ballymacarbry, Clonmel, Co. Tipperary. This will be administered via the Aerogen solo nebuliser every 6 h from enrolment to day 10, in addition to the standard care required as determined by the treating team. Participants assigned to ‘standard care’ will receive the standard care required as determined by the treating team and will not be treated with nebulised heparin.

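### The co-primary d-dimer AUC starts on day 1 in the outcome definition but on day 0 in the sampling schedule, and the first sample's timing relative to the first dose is not stated.

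*Protocol article*

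**What the plan says.** All places are in the protocol article.

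- **Outcomes {12}** defines the first co-primary outcome as the between-group difference in d-dimer AUC on days 1, 3, 5 and 10. The same four days are repeated for the AUC of the other inflammatory and coagulation markers.
- **Abstract, Methods** gives the same list: "These parameters will be assessed on days 1, 3, 5 and 10". The items just before that sentence are secondary and safety measures. D-dimer is not named among them, so this supports the day-1 list for the other markers more directly than for d-dimer.
- **Participant timeline {13}**, under days 0 to 10, plans blood samples for inflammatory markers and "coagulation parameter assessment as per the primary and secondary outcomes, on days 0, 3, 5 and 10".
- The same section describes day 0 as "screening, consent/next of kin assent, enrolment and randomisation" and lists day 1 separately, as the day of the baseline eCRF.
- **Intervention description {11a}** gives heparin "every 6 h from enrolment to day 10".
- **Eligibility criteria {10}** requires "D-dimers > 200 ng/ml" for entry.
- **Sample size {14}** bases power on d-dimer alone.

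**The concern.** The timeline points back to the outcomes and then gives a different first day. A site that follows the timeline draws no day-1 sample, and an analyst who follows the outcome definition uses no day-0 value. Days 3, 5 and 10 agree.

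The first day matters because enrolment and the start of dosing both fall on day 0. The choice between day 0 and day 1 can decide whether the AUC begins at an untreated value or at one taken after treatment began. These are different estimands. If a post-dose first value were later used as a baseline, by adjustment or subtraction, part of any early treatment effect would be removed. If some patients or sites follow one passage and some the other, the raw AUC also varies with the length of the window.

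**Working it through.** **Inputs.** Sampling days from Outcomes {12} (1, 3, 5, 10) and Participant timeline {13} (0, 3, 5, 10). ICU mean 944.8 ng/ml with SD 485.3, and ward mean 436.5 ng/ml, from Sample size {14}. A six-hour dosing interval from Intervention description {11a}. The article gives no AUC figure to reproduce.

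**1. Trapezoid weights.** The first sample has weight (t2 − t1)/2, each middle sample (next − previous)/2, and the last (t4 − t3)/2.

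| Grid | Weights (days) | Window | First sample's share |
|---|---|---|---|
| 0, 3, 5, 10 | 1.5, 2.5, 3.5, 2.5 | 10 | 1.5/10 = 15.0% |
| 1, 3, 5, 10 | 1.0, 2.0, 3.5, 2.5 | 9 | 1.0/9 = 11.1% |

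**2. Scale, for a constant level of 944.8 ng/ml.**
- Day-0 start: 944.8 × 10 = 9,448 ng/ml × days.
- Day-1 start: 944.8 × 9 = 8,503 ng/ml × days.
- The day-0 grid is 11% higher (10/9 = 1.111). Divided by its own window, each AUC returns 944.8, so the gap is one of scale only.

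**3. Noise from mixing the grids (illustration).** Assume each patient has a constant level L with mean 944.8 and SD 485.3, and that half the patients, unrelated to L, are on each grid. The window W then has mean 9.5, mean square (81 + 100)/2 = 90.5 and variance 0.25.
- Var(W × L) = 485.3² × 90.5 + 944.8² × 0.25 = 21,314,206 + 223,162 = 21,537,368, so SD = 4,641.
- A common 9.5-day window gives SD = 9.5 × 485.3 = 4,610.
- The increase is about 0.7%: avoidable, but small.

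**4. Effect on the estimand (limiting case).** Suppose treatment lowers every post-dose value by the planning difference, 944.8 − 436.5 = 508.3 ng/ml, in full by day 1.
- A grid starting with a post-dose day-1 sample gives a time-averaged difference of 508.3.
- A grid starting with a pre-dose day-0 sample puts 15% of its weight on a value treatment cannot have changed, giving 0.85 × 508.3 = 432.1.

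Dividing by the window does not remove this difference. A slower onset of effect would alter both figures.

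**5. Timing against dosing.** If the first dose is given at enrolment, a sample 24 h later follows about 24/6 = 4 doses. A day-0 sample could fall on either side of the first dose. No section fixes this.

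**The case against.** **The labels may mean the same thing.** Several items filed under day 1 in the timeline are values taken nearest to, and before, randomisation. Day 1 may therefore be partly a label for baseline. This is plausible but not established: d-dimer is not among those items, days 0 and 1 are separate entries, and nothing equates them.

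**An article may leave exact draw times to the full protocol.** That is fair for clock times. It does not cover two sections of one article that name different days for the same samples.

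**The arms are affected alike.** This stands. A common schedule, whichever it is, does not by itself bias the contrast. A reader might infer an 11% distortion of the treatment effect from the two AUC totals, but those totals differ only because one level is multiplied by 9 or by 10.

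**A pre-treatment value should exist.** A reader might infer that a day-1 start leaves the trial with no pre-treatment d-dimer. The documents do not support that. Entry requires a d-dimer above the threshold, and Implementation {16c} has screening data entered before randomisation is requested. The remaining gap is that this value is not named as the baseline and its timing is not given.

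**No baseline adjustment is planned.** The covariates given as examples in Statistical methods {20a} do not include d-dimer, so harm from adjusting for a post-dose value is a risk to guard against and not a stated plan.

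**Conclusion.** The inconsistency holds. It is in the current text and concerns the only powered endpoint. The AUC has a 9-day or a 10-day window, and its first sample carries 11% or 15% of the weight. It should be fixed before analysis.

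The consequence is an unfixed estimand, with some avoidable noise if the grids are mixed. It is not a demonstrated bias. The scale result assumes a constant level and the trapezoid rule. The four-dose figure assumes dosing starts at enrolment and the sample is taken 24 h later.

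A reader might also infer that the article contradicts itself on whether the first sample precedes dosing. It does not: that point is unspecified. A day-1 sample is probably post-dose, and a day-0 sample is not guaranteed to be pre-dose.

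**What to change.** 1. Reconcile Outcomes {12}, Participant timeline {13} and the day list in the Abstract to one first sampling day.
2. State when that sample is taken relative to randomisation and first dose, with an equivalent timing rule for controls, who have no first dose.
3. Compute the AUC divided by the observed interval, using actual sampling days or times where they were recorded. The article does not say that draw times are captured, so check this first. Dividing by the interval puts samples from either grid on one scale, but it does not make a post-dose value a baseline.
4. Use a pre-randomisation d-dimer as the baseline covariate: the day-0 sample where it was taken before the first dose, otherwise the screening value required for eligibility. Do not adjust for, or subtract, a first sample taken after dosing began.

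The cost is wording, a check of recorded sampling times and retrieval of the screening values. No new sample is needed, which matters because Trial status expected recruitment to end in Spring 2022. The choice should be documented before the data are analysed by arm.
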